### Recruitment {15}

Our patients will be chosen from the cases referred to the specialized CF clinic at Akbar Children’s Hospital, which covers all the CF patients in our regional state. The initial data is available on the CF registry for easier access. The patients are also supported by the local CF association.

## Assignment of interventions: allocation

### Sequence generation {16a}

The participants of the study who followed the inclusion criteria were divided into two groups: nanomicelle fat-soluble vitamins oral drops as the intervention group and the standard form of fat-soluble vitamins as the control group. Special websites for randomization are used in order to allocate participants into two groups.

### Concealment mechanism {16b}

According to the obtained sequence, the trial researchers will put the codes in the sealed opaque envelopes in order, and when the patients visit the clinic, one envelope is taken in order, and according to the code written in it, the patient is placed in the intervention or control group.

### Implementation {16c}

The main researcher will perform the generation of the allocation sequence, the enrollment of participants, and the assignment of participants to interventions.

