### Eligibility criteria {10}

#### Inclusion criteria

The inclusion criteria of the study include (1) one or more typical phenotypic features of CF and a minimum of an elevated sweat chloride concentration on two/more occasions or two mutations known to cause CF on separate alleles, (2) age ≥ 8 years old, (3) gastrointestinal and pulmonary involvement, (4) the oxygen saturation percentage based on the pulse oximetry of ≥ 90% at room temperature, (5) a clinically stable situation, and (6) informed consent of the patient’s parents.

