#### Exclusion criteria

The exclusion criteria of the study include (1) cardiovascular, renal, or hepatic impairment; (2) celiac disease; and (3) no adherence to drug consumption.

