## Assignment of interventions: blinding

### Who will be blinded {17a}

Due to the distinguishable appearance of the drugs used in the intervention and control groups, both participants and the main researcher are aware of the group assignments for the patients. However, the data analyst and the nutritionist, responsible for regular communication through weekly phone calls and monthly in-person visits, are blinded to the trial details. In clinical trial studies, the term “blinded” typically applies to patient involvement. In this study, only the data analyst and the nutritionist, who assess patients, operate under blind conditions. Consequently, the trial is registered as “not blinded” in accordance with standard practices in clinical trial blinding.

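### One main researcher generates the sequence, enrols and assigns, so the envelopes do not assure concealment from the person who enrols

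*Protocol article*

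**What the plan says.** The allocation procedure is spread over three short sections of the protocol article.

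- **Sequence generation {16a}:** "Special websites for randomization are used in order to allocate participants into two groups". No central service or independent holder of the list is named.
- **Concealment mechanism {16b}:** working from the sequence obtained, "the trial researchers will put the codes in the sealed opaque envelopes in order". On how the envelopes are then used, the section says that "when the patients visit the clinic, one envelope is taken in order". The code inside decides the arm.
- **Implementation {16c}:** "The main researcher will perform the generation of the allocation sequence, the enrollment of participants, and the assignment of participants to interventions".

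Two other sections bear on the point. One of the inclusion criteria is "a clinically stable situation", which the article does not define. Trial status reports that recruitment ran from July 24 to November 30, 2022, and is complete.

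**The concern.** Allocation concealment has one purpose: whoever decides that a patient enters must not be able to know which arm comes next. An opaque sealed envelope does this for anyone who has not seen the ordered list. It cannot do so for someone who produced that list and can count how many envelopes have been used. Implementation {16c} puts these two positions in one person.

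What is at stake is selection bias before randomisation takes effect. A patient could be judged stable today or asked to return later, depending on the arm that is due. The Recruitment {15} section adds opportunity: the clinic serves every CF patient in the region, and background data are on a registry, so candidates are known in advance. An intention-to-treat analysis, as planned in {20c}, preserves the groups as they were formed. It does not repair groups that were formed selectively.

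**Working it through.** The point is one of roles and carries no figure of the plan to reproduce. The sections are set side by side.

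1. **Who has produced the ordered list?** The main researcher ({16c}), with the help of a randomisation website ({16a}).
2. **Does the envelope order follow that list?** Yes. The envelopes are filled in sequence order and taken in the same order ({16b}). Position in the list therefore determines the content of the next envelope.
3. **Who enrols and assigns?** The same main researcher ({16c}).
4. **Is there a step that separates this person from the list?** Sections {16a} to {17b} contain none: no pharmacy, no central release, no independent custodian, and no statement that the list was handed over after generation.
5. **Does entry leave room for judgement?** Yes, at least through the clinical-stability criterion.

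Steps 1 to 3 mean that foreknowledge by the enrolling person is possible. Step 4 means that nothing written rules it out. Step 5 means that foreknowledge could influence who enters.

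**Route into the primary result.** Statistical methods {20a} plans independent t-tests or Mann-Whitney tests between groups and names ANCOVA for the secondary outcomes only. Suppose steering shifts the mean baseline vitamin level between arms by d standard deviations, the baseline-to-3-month correlation is r, and the standard deviations at the two times are equal. Then:

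- an unadjusted comparison of 3-month levels is biased by r × d;
- a comparison of changes from baseline is biased by r × d − d = (r − 1) × d, that is, in the opposite direction when r lies between 0 and 1;
- ANCOVA on the baseline level removes the part of the bias that runs through the measured baseline, if the relation is linear.

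The article gives neither d nor r, so no number can be attached. The algebra shows only why baseline adjustment is relevant and where it stops: a shift in a trait that is not measured at baseline passes through all three analyses.

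**Effect on sample size.** None. The 33 per group, 37 after the dropout allowance and 74 in total do not depend on who holds the list.

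**The case against.** The strongest reply is that a journal article condenses the full protocol, and custody of the list may be described there. That would answer silence. It does not answer {16c}, which positively gives all three tasks to one person.

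Several stronger readings are tempting, and the article does not support them.

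- **That the envelopes conceal nothing, or that the design has no concealment at all.** A website produces the sequence, and {16b} has the trial researchers, in the plural, fill the envelopes. Patients, parents and any staff who have not seen the list may well be kept unaware. Only concealment from the enrolling person is in doubt.
- **That the main researcher knew the next allocation.** The article does not say that this person kept or consulted the list. Foreknowledge is an inference from having generated it. The defensible statement is that it is not excluded.
- **That the open-label design proves the point.** Who will be blinded {17a} says that "both participants and the main researcher are aware of the group assignments for the patients", but it gives the visible difference between the products as the reason. That is knowledge after assignment, a blinding matter, and it is not evidence about concealment.
- **That the exclusion for "no adherence to drug consumption" is a second discretionary entry gate.** The only adherence definition, use of less than 70% of the drugs in {11c}, concerns study members taking trial medication, so this exclusion may apply during the trial. The point does not rely on it.

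It is also fair to say that the criteria sections do not name who judges stability. That it is the main researcher follows from the enrolment task in {16c}.

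**Conclusion.** The point holds in limited form. As written, the procedure does not assure concealment from the person who enrols, because generation, enrolment and assignment rest with one main researcher and the envelopes follow that person's list in order. Selection bias is therefore possible. Whether it occurred, and how large it would be, cannot be determined from the article.

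The conclusion rests on two assumptions: that generating the list gives access to its content, and that the person who enrols also applies the stability criterion. Nothing in the article contradicts either. A statement that the list passed to someone else before the first enrolment, and that the main researcher no longer had access to it, would largely settle the matter.

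**What to change.** **For this cohort**, recruitment is closed and the procedure cannot be changed. Three things remain:

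1. State who generated the list, who filled and held the envelopes, and whether the main researcher had access to the list while enrolling.
2. If the roles were not separated, limit the concealment claim to those from whom the sequence was in fact hidden, and acknowledge the risk of selection bias as a limitation.
3. Extend the ANCOVA in {20a} to the primary outcome, with the baseline level of the same vitamin as covariate for each of A, D, E and K. State in the same place that this corrects only imbalance in the measured baseline level and not steering on unmeasured traits such as adherence.

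**For any further recruitment or a later trial**, reword {16b} and {16c} so that an existing function that neither enrols nor treats, such as a hospital pharmacy, generates and holds the list and the numbered envelopes. The next envelope is opened only after consent, eligibility and baseline measurements have been recorded.

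**Cost.** For this cohort, a few sentences and one more use of a method already planned, on baseline samples that the plan already collects. For later recruitment, the hand-over of one task, assuming that such a function is available at the site. Sample size and follow-up are unchanged.

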## Assignment of interventions: blinding

### Who will be blinded {17a}

Due to the distinguishable appearance of the drugs used in the intervention and control groups, both participants and the main researcher are aware of the group assignments for the patients. However, the data analyst and the nutritionist, responsible for regular communication through weekly phone calls and monthly in-person visits, are blinded to the trial details. In clinical trial studies, the term “blinded” typically applies to patient involvement. In this study, only the data analyst and the nutritionist, who assess patients, operate under blind conditions. Consequently, the trial is registered as “not blinded” in accordance with standard practices in clinical trial blinding.

### Procedure for unblinding if needed {17b}

As mentioned, there is no possibility of blinding researchers and patients due to the type of intervention, so this item is not applicable to this study.

## Data collection and management

### Plans for assessment and collection of outcomes {18a}

As the primary outcome of the present study, the serum level of fat-soluble vitamins will be measured by the laboratory test using the HPLC method. To ensure the quality of the employed laboratory methods, the performance specifications will be verified before using the kits for the analysis of the patient’s samples. All the tests will be carried out in duplicate, and the conventional curve will be prepared using the serial dilutions of the standard samples. The secondary outcomes of the present study are anthropometric assessments, which will be performed in a standard position using SECA instruments for height and weight. Additionally, the WHO growth standard charts will be used for the evaluation of the BMI *Z*-score. The clinical symptoms will be obtained by the Shwachman-Kulczycki score, and the children’s quality of life will be assessed by Health-Related Quality of Life in Children with Cystic Fibrosis to investigate the role of fat-soluble vitamins in the lives of CF patients.

### Plans to promote participant retention and complete follow-up {18b}

Because of the fact that most of the patients are from the pediatric population, we will ask their parents to provide written feedback on the observed outcomes of the evaluations in their children in addition to regular follow-up by phone calls or free-of-charge visits. Also, the nanomicelle fat-soluble vitamins oral drops are provided to the patients at no cost.

### Data management {19}

In the current trial, the database will be created from the questionnaire of clinical data and laboratory assay results in Excel software and SPSS. The trial researchers will collect the data at the beginning and during the follow-up and record the obtained data in the paper checklists as well as the designed Excel datasheet. Next, the data will be analyzed in SPSS. To ensure security, the login password is allowed only for the trial researchers. The database will only accept the variables that are consistent with the previous entries, and it could also be altered in the case of randomly missing values. Semimonthly, 10% of the electronic data will be randomly compared with the paper questionnaires.

### Confidentiality {27}

Participant data, laboratory specimens, collected data, and reports will be identified by a coded ID number. Data collected during the course of the research will remain strictly confidential and only be accessed by the research team. Additionally, the unidentified data will be shared with other researchers to allow international prospective meta-analyses.

### Plans for collection, laboratory evaluation, and storage of biological specimens for genetic or molecular analysis in this trial/future use {33}

This intervention does not involve the storage of biological specimens for genetic or molecular analysis

## Statistical methods

### Statistical methods for primary and secondary outcomes {20a}

SPSS will be used to analyze the data. The Kolmogorov-Smirnov test will be used to evaluate data distribution. The data are expressed as frequencies and percentages for the qualitative variables, the mean and standard deviation for the normally distributed continuous variables, and the median and interquartile range for the other variables. Additionally, intergroup differences will be evaluated using a paired *T*-test for the normally distributed continuous variables and the Wilcoxon rank-sum test for the other continuous variables. Intergroup differences will be assessed using an independent *T*-test for the normally distributed continuous variables and the Mann-Whitney *U*-test for the other quantitative variables. The mean changes in the secondary outcomes will also be adjusted using the analysis of covariance (ANCOVA). The *P* value of less than 0.05 will be considered significant in all the numerical analyses.

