## Introduction

### Background and rationale {6a}

Cystic fibrosis (CF) is a life-shortening, autosomal recessive genetic disorder, and the most common inherited disease in Caucasians. The disease prognosis has improved considerably in recent decades with the advanced treatments, and the mortality rate has been reduced by 2% annually. The average age of survival in CF patients has been reported to be 65 years in men and 56 years in women [1]. CF is caused by mutations in the cystic fibrosis transmembrane conductance regulator (CFTR) gene, resulting in impaired pancreatic function and, as a result, reduced intestinal absorption of lipids and fat-soluble vitamins, particularly in patients with CF developing pancreatic insufficiency [2]. Fat-soluble vitamins deficiency is still a current therapeutic challenge in CF, chronic pancreatitis, and biliary atresia. A large number of patients exhibit vitamin K or D insufficiencies, and the prevalence of vitamin E and A deficiencies is also significant despite full compliance [3]. In many cases, increases in vitamin dosage are not efficacious, and intractable fat-soluble vitamin deficiencies are diagnosed in CF patients, raising the issue of whether modern drug delivery methods could improve the condition of patients [3, 4]. Although the standard formulation is still used in CF patients, there are new delivery technologies, such as the liposomal form of vitamin E, the nanomicelle form of curcumin, and specific carotenoids [5]. To improve stability and increase the solubility of fat-soluble or poorly water-soluble compounds, several strategies such as liposomal, nanoliposomal, and micellar forms have been recommended. One is using nanomicelles which are efficient tools to encapsulate the drugs with a low aqueous solubility [6]. The nanomicelle has a core-shell structure that prevents the penetration of water in its inner core creating an appropriate environment for the encapsulated drug versus the free drug [6]. Other advantages of micelles as drug carriers include facilitated transport through biological barriers, protection against degradation, being cost-effective, and increased solubility in aqueous media that include the unstirred water layer of the intestine [7]. Consequently, the concept of using the nanomicelle formulation of fat-soluble vitamins could be admirable in CF patients through the facility of absorption of nano-sized vitamins and the lack of necessity of the presence of pancreatic enzymes for their absorption process. In this study, we focused on a novel nanomicelle formulation of vitamins A, D, E, and K, and the main purpose was to address the problem of intractable fat-soluble vitamin deficiencies in pancreatic-insufficient CF patients. The present study aimed to evaluate the efficiency of the novel nanomicelle formulation of fat-soluble vitamins in CF (Table 1).

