### Outcomes {12}

The primary outcome of the current trial is the measurement of the serum levels of fat-soluble vitamins once at the onset of enrollment and once at the end of the trial after 3 months.

The secondary outcomes are clinical criteria evaluation by the Shwachman-Kulczycki score (an index to evaluate the severity of the disease in CF patients, which includes general activity, physical examination, nutrition, and radiological findings), anthropometric assessment by the BMI *Z* score, and quality of life evaluation by using the CFQ (Health-Related Quality of Life in Children with Cystic Fibrosis) from the baseline to 3 months of the intervention (Fig. 1).

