### Sample size {14}

Due to the lack of clinical trials on the evaluation of the efficacy of nanomicelle formulation of fat-soluble vitamins in children with cystic fibrosis, we use the researcher’s experience to estimate the sample size. According to this, about 60% of CF patients who use the routine formulation of fat-soluble vitamins are treated for vitamin D deficiency. It is estimated that the new method will increase the recovery rate by 30–40%. Considering alpha = 0.05 and power = 80%, the minimum required sample size in each group is estimated to be 33 people. By considering the 10% dropout rate for the sample, a total of 37 samples for each group was calculated. In total, 74 patients with CF are needed to be included in the randomization aspect of this research.

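### Four unranked primary vitamin levels, each judged at P < 0.05 with no success rule: if any one may carry the claim, its false-positive rate is about 13% to 18.5%

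*Protocol article*

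**What the plan says.** Outcomes {12} defines the primary outcome in the plural: "The primary outcome of the current trial is the measurement of the serum levels of fat-soluble vitamins", taken at enrolment and at 3 months. Background and rationale {6a} identifies the vitamins, describing "a novel nanomicelle formulation of vitamins A, D, E, and K". None is placed first. No composite, testing order, division of alpha or requirement that all four succeed is given.

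Statistical methods for primary and secondary outcomes {20a} compares the arms one variable at a time: "Intergroup differences will be assessed using an independent *T*-test for the normally distributed continuous variables and the Mann-Whitney *U*-test for the other quantitative variables". The same section closes by declaring that a P "value of less than 0.05 will be considered significant in all the numerical analyses", and Methods for additional analyses {20b} repeats that rule.

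Sample size {14} refers to one vitamin only. Its starting point is that "about 60% of CF patients who use the routine formulation of fat-soluble vitamins are treated for vitamin D deficiency", and it plans on a single test: "Considering alpha = 0.05 and power = 80" per cent, giving 33 per group, or 37 after 10% dropout.

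**The concern.** The trial is sized as if there were one primary test, while the analysis section provides four, each at the full 5%. Objectives {7} frames a single efficacy claim about the formulation. Nothing in the text tells a reader which pattern of four results would support that claim.

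One vitamin at P = 0.04 with three null results could be presented as a positive trial, and the vitamin carrying the conclusion could be chosen after the data are seen. On that use of the results, the 5% level attached to each test is not the error rate of the primary claim.

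**Working it through.** **Inputs.** Four vitamins ({6a}, {12}). One between-group test per vitamin at 0.05 ({20a}). For power: 60% recovery on the routine formulation, alpha 0.05, 80% power and 33 per group ({14}). Assumed because the protocol does not say: two-sided tests, the improvement read as 30 percentage points (60% to 90%), and all correlations between vitamins.

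**1. The plan's own figure.** Two proportions, pooled variance, mean proportion 0.75:

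n = [1.960 × √(2 × 0.75 × 0.25) + 0.842 × √(0.6 × 0.4 + 0.9 × 0.1)]² / 0.30² = (1.200 + 0.483)² / 0.09 = 31.5, so 32 per group.

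This is within one of the stated 33. Dropout: 33 / 0.9 = 36.7, so 37 per group and 74 in total, as stated. Power with 33 per group is Φ[(0.30 × √33 − 1.200) / 0.574] = Φ(0.911) = 81.9%. The sample size is thus consistent with one test, on one vitamin, at 0.05.

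**2. Error rate if any one of four suffices.** With no true effect on any vitamin and independent tests:

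- either direction: 1 − 0.95⁴ = 18.5%
- in favour of nanomicelle only: 1 − 0.975⁴ = 9.6%, against 2.5% for one test
- ceiling under any dependence, either direction: 4 × 0.05 = 20%

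Simulation of four equally correlated normal test statistics (2,000,000 draws each):

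| Assumed correlation | Either direction | Favouring nanomicelle |
|---|---|---|
| 0.3 | 17.4% | 8.7% |
| 0.5 | 15.6% | 7.8% |
| 0.7 | 13.0% | 6.5% |
| 0.9 | 9.4% | 4.7% |

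**3. Error rate under the opposite rule.** If all four vitamins had to be significant, the error rate could not exceed the 5% of a single test, so there would be no inflation.

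**4. Cost of control.** Holm starts at 0.05 / 4 = 0.0125, where the two-sided critical value is 2.498. On the 60% versus 90% inputs with 33 per group, power is Φ[(0.30 × √33 − 2.498 × 0.612) / 0.574] = Φ(0.337) = 63.2%, down from 81.9%. This is a floor for the vitamin concerned, because later Holm steps use less strict levels. To restore 80% at 0.0125 would take (1.530 + 0.483)² / 0.09 = 45.0, rounded up to 46 per group. That is 52 after dropout and 104 in total.

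**The case against.** The strongest objection is that the inflation follows from a decision rule the protocol never states. If all four vitamins must succeed, alpha holds. If each vitamin is reported as its own question, whether to control the family-wise rate is a matter of debate rather than an error. This stands, and it makes the size of the problem conditional. It does not remove the point: the text excludes none of these readings, and the objective is worded as one claim about the formulation.

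A reader might infer that the trial's false-positive rate simply is 18.5%. The documents do not support that. The figure needs both the any-one rule and independence. The Discussion describes a shared absorption route for these vitamins, which makes positive correlation plausible, and the figure also counts errors in favour of the control arm. Nor does {14} allocate the 5% to vitamin D; it uses 0.05 as a planning input.

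It may also be said that an analysis plan not shown here could deal with multiplicity. It could supply a success rule, but a correction would contradict the protocol's explicit threshold for every analysis. This is a rule stated badly, not a detail left out.

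The commitment to publish whatever the direction of effect (Dissemination plans {31a}) limits selective publication. It does not limit selective emphasis among four primary results.

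**Conclusion.** The point holds in conditional form. Four vitamin levels form one unranked primary outcome without a success rule, and {20a} fixes an uncorrected 0.05 for each. If any one may be claimed as primary success, the family-wise rate is 18.5% under independence and about 13% to 17% for assumed correlations of 0.7 to 0.3. In favour of nanomicelle alone it is 9.6% at zero correlation, against 2.5% for one test. These figures assume two-sided tests and one between-group test per vitamin; claims drawn from within-group tests at 0.05 would add to them.

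This should be corrected, but it does not invalidate the design. The defect is that the protocol permits the inflated reading, not that it commits to it.

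**What to change.** Before any group comparison is seen, replace the blanket threshold in {20a} and {20b} with a stated rule for the primary family. Two rules would serve:

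- **Holm across the four between-group vitamin tests**, at an overall two-sided 0.05. This keeps the primary outcome as stated. The cost is the first step at 0.0125, with about 63% power instead of 82% on the protocol's own inputs.
- **A fixed sequence starting with vitamin D**, the only vitamin used in the sample size, at two-sided 0.05, with A, E and K tested under Holm only if D is significant. The first test keeps its full level. The cost is that a positive A, E or K alone is no longer primary success.

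Under either rule, report all four vitamins with 95% confidence intervals.

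This is more than a wording change. Trial status records recruitment as complete on November 30, 2022, with procedures due to end by April 2023. Ordering or demoting stated primary vitamins is a substantive outcome change, so either route needs ethics approval (see {25}) and a registry update. If the rule is set after results are seen, it must be disclosed as post hoc.

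Putting vitamin D first does not by itself align the sample size with the endpoint: {14} is built on a binary recovery rate, whereas {12} measures serum levels. That mismatch needs separate attention.
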